### Internet-Based Mind-Body Training Programs

For this study, we developed 2 asynchronous, 8-week online mind-body training programs: the iMBSR and the iLifeEd training programs. Both programs were provisionally adapted from our standardized MBSR and lifestyle education manuals, which have previously been used to conduct Stage II efficacy studies of mindfulness meditation [24,62]. Our team’s expertise in contemplative sciences, RCTs, and psychosocial interventions was complemented by instructional design expertise from the Office of Distance Education at The Ohio State University. In designing these platforms, we ensured inclusion of the critical components of the MBSR and lifestyle education program, including didactics, experiential learning, homework practices, social support and community building, and facilitator interactions. We additionally conducted focus groups with our target population, adults aged older than 50 years with SCD, to better understand their perspectives on healthy living, brain health, and engagement with digital interventions for improving brain health. Themes from the focus groups (N=23) were incorporated throughout the platforms, resulting in the final versions of the iMBSR and the iLifeEd programs.

The iMBSR and iLifeEd programs are delivered through The Ohio State University’s Canvas for Continuing Education platform. Each program consists of 8 modules, with each module requiring approximately 2 hours per week to complete. Participants are expected to complete 1 module per week over 8 weeks. In addition, they are invited to optional weekly drop-in hours with the study PI, a licensed psychologist with more than 17 years of experience facilitating mind-body interventions.

The 2 programs are matched on the following metrics: (1) format of delivery,—both programs are online and quasi–self-paced; (2) timing—each of the 8 modules for the 2 programs is expected to take 2 hours per week, plus optional 30-minute drop-in hours; (3) content—both programs have been designed to integrate didactics, experiential practices, and homework practices; and (4) peer support—participants in both groups have access to a community board for discussions following experiential practices. The community boards are expected to foster a sense of community throughout the program. Table 2 outlines the themes of each module for both programs and provides an overview of the content covered in each module.

**Table 2. T2:** Weekly themes, practices, and homework assignments for each of the 8 weeks of the internet-based mindfulness-based stress reduction (iMBSR) and internet-based lifestyle education (iLifeEd) programs developed for the internet-based mind-body training study.

	iMBSR	iLifeEd
Module 1	The potential of mindfulness meditation Pt^a^ 1. Introduction to study aims (40 min) Pt 2. Defining mindfulness (45 min) Pt 3. Putting it into practice! (30 min) Hw^b^ 1. Mindful eating (15 min*)* Hw 2. Body scan practice (15 min*)*	Introduction to the study Pt 1. Introduction to study aims (45 min) Pt 2. Shift from the biomedical model to the biopsychosocial model (40 min) Pt 3. Watch, reflect, and apply! (40 min) Hw 1. Blue zones (20 min) Hw 2. Stretching and toning (15 min) Hw 3. On health literacy (5 min)
Module 2	Breath as our ever-present anchor Pt 1. Cultivating awareness by tuning into our bodies (35 min) Pt 2. Cultivating mindful awareness with the breath (50 min) Pt 3. Putting it into practice! (30 min) Hw 1. Body scan practice (15 min) Hw 2. Breath awareness practice (15 min)	All about sedentary behavior Pt 1. Introduction to sedentary behavior (40 min) Pt 2. Benefits of sitting less (30 min) Pt 3. Watch, reflect, and apply! (30 min) Hw 1. Posture for back pain (5 min) Hw 2. Stretching and toning (15 min) Hw 3. Move more, sit less (10 min)
Module 3	Mindful awareness of sensations Pt 1. Invitation to taking your seats (30 min) Pt 2. Cultivating awareness through mindful yoga (45 min) Pt 3. Putting it into practice! (35 min) Hw 1. Breath awareness practice (20 min) Hw 2. Mindful movement (15 min)	All about physical activity Pt 1. Introduction to physical activity (30 min) Pt 2. Benefits of physical activity and practical tips (35 min) Pt 3. Watch, reflect, and apply! (35 min) Hw 1. Exercising for brain health (5 min) Hw 2. Stretching and toning (15 min) Hw 3. Motivation for exercise (15 min)
Module 4	Mindful of emotions: impact on stress Pt 1. Understanding and experiencing emotions (35 min) Pt 2. Introduction to stress (45 min) Pt 3. Putting it into practice! (30 min) Hw 1. Mindful movement (15 min) Hw 2. Sitting meditation practice (15 min)	On brain plasticity Pt 1. Brain plasticity and cognitive reserve (40 min) Pt 2. Benefits of cognitively stimulating activities (30 min) Pt 3. Watch, reflect, and apply! (35 min) Hw 1. More on neuroplasticity (15 min) Hw 2. Stretching and toning (15 min) Hw 3. Interview with Yaakov Stern: founder of cognitive reserve (5 min)
Module 5	Finding the space to make choices Pt 1. Introduction to choiceless awareness (55 min) Pt 2. How do we contribute to our own stress? (25 min) Pt 3. Putting it into practice! (30 min) Hw 1. Choiceless awareness practice (15 min) Hw 2. Body scan practice (15 min)	All about sleep Pt 1. Introduction to sleep (40 min) Pt 2. Risks associated with sleeping less (35 min) Pt 3. Watch, reflect, and apply! (30 min) Hw 1. Busting sleep myths (5 min) Hw 2. Stretching and toning (15 min) Hw 3. One more reason to get good sleep (10 min)
Module 6	Firming and stabilizing your practice Pt 1. Deepening your meditation practices (45 min) Pt 2. More on breath awareness (40 min) Pt 3. Putting it into practice! (30 min) Hw 1. Standing movements (15 min) Hw 2. Choiceless awareness practice (15 min)	All about stress Pt 1. Introduction to stress (45 min) Pt 2. Coping with stress (25 min) Pt 3. Watch, reflect, and apply! (35 min) Hw 1. Why you need stress in your life (15 min) Hw 2. Stretching and toning (15 min) Hw 3. Mindfulness to reduce stress (5 min)
Module 7	Kindness toward self and others Pt 1. Starting with foundational practices (45 min) Pt 2. Practicing loving-kindness meditation (40 min) Pt 3. Putting it into practice! (30 min) Hw 1. Mindful yoga (15 min) Hw 2. Any 15-minute practice (15 min)	All about diet Pt 1. Introduction to diet – Focus on nutrition (45 min) Pt 2. Introduction to diet – Focus on hydration (35 min) Pt 3. Watch, reflect, and apply! (35 min) Hw 1. Why we can’t stop eating unhealthy foods (15 min) Hw 2. Stretching and toning (15 min) Hw 3. Dehydration with aging (5 min)
Module 8	Mindfulness: a lifelong practice! Pt 1. Returning to the basics (30 min) Pt 2. Final closing (50 min) Pt 3. Building your personalized mindfulness practice (30 min) Hw 1. Any 15-minute practice (15 min) Hw 2. Any 15-minute practice (15 min)	All about social support Pt 1. Introduction to social engagement and social support (30 min) Pt 2. Social engagement – Risks and practical strategies (20 min) Pt 3. Watch, reflect, and apply! (45 min) Hw 1. What makes a good life? (15 min) Hw 2. Stretching and toning (15 min) Hw 3. The value of human connection (15 min)

a Pt: part.

b Hw: homework.

### Primary Outcomes

Feasibility will be determined by evaluating the recruitment and retention of study participants, with high feasibility defined as the successful recruitment and enrollment of 60 participants and an attrition rate of no greater than 25%. We will also examine changes in SCD, with reductions on the ECog Questionnaire considered as evidence for feasibility of the intervention. Acceptability will be measured using the Acceptability of Intervention Measure [63], with high acceptability defined as an average score greater than 3 (on a 1‐5 scale, ranging from “completely agree” to “completely disagree”). Program satisfaction will be measured by our custom Postintervention Acceptability Questionnaire, which focuses on program enjoyment, satisfaction, and potential barriers. High program satisfaction will be defined as an average score greater than 5 (on a 0‐10 scale, ranging from “not at all” to “extremely” scale) for items focused on satisfaction. Participant attendance will also factor into acceptability, with high participation defined as at least 50% of participants successfully completing 6 or more modules on the class platform Scarlet Canvas.

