**Objective:**

This randomized controlled trial aims to evaluate the feasibility and acceptability of an internet-based, asynchronous mindfulness-based stress reduction program compared with an active control group (an internet-based lifestyle education program). Secondary objectives include examining preliminary effects of each intervention on SCD, plasma-based biomarkers of amyloid and tau pathology, and everyday mind-wandering.

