### Participant Eligibility

The target population for this study is adults aged older than 50 years with SCD. Following the criteria identified in a study by Jessen et al [43] to recruit participants with SCD, we will administer the ECog Questionnaire to quantify self-reported deficits in cognitive functioning. The ECog Questionnaire is a self-reported and an informant-reported 39-item questionnaire assessing cognitively based everyday activities [41]. This measure was recently found to be reliable and valid in an ethnoracially diverse sample of older adults, with scores on this measure correlating reliably with concurrent and longitudinal changes in cognition and brain volumes [44]. In the proposed study, we chose to use the self-reported ECog Questionnaire to reduce participant burden. Emerging evidence suggests that inclusion criteria requiring input from informants, such as family members, disproportionately exclude traditionally underrepresented groups, including individuals with low socioeconomic status and those from racial and ethnic minority backgrounds [45,46]. Furthermore, for this study, we will use the previously validated cutoff score of 1.31 to recruit participants with SCD. This cutoff has been independently validated in 2 separate studies [47,48], with individuals scoring greater than 1.31 on the self-reported ECog twice as likely to be diagnosed with MCI [47]. Only participants with elevated scores (>1.31) will be invited for an assessment of objective cognitive performance.

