### Sample Size and Power

Our feasibility study will involve 60 adults with SCD randomized to one of 2 groups: iMBSR or iLifeEd. Our primary outcome variables for this study are the feasibility and acceptability of the protocols. With 30 participants per group, we will be able to estimate within-group feasibility percentages (eg, the percentage of participants who find the program prospectively acceptable and the percentage of people who indicate adequate levels of satisfaction) with a margin of error of no larger than +18% or −18%. For intervention adherence, we will have 80% power for detecting a proportion of greater than 50% adherence if the true proportion of participants who complete all modules is 75%.

Our key secondary outcome variables for this study are the plasma Aβ_42_/Aβ_40_ ratio and plasma p-tau217, quantifying reduction in amyloid and tau pathology following training. We conducted sensitivity analyses to determine the effect size that we would need to observe to detect significant effects. Specifically, with 30 participants per group, we would need to observe a large effect size (Cohen *d*=0.74) to detect significant effects. Although there are, to our knowledge, no mindfulness-based interventions examining effects on plasma-based measures of amyloid and tau, prior work by one of the co-authors (EH) has demonstrated that 4 weeks of slow-paced breathing significantly decreases plasma Aβ_42^,^_ with a large effect size (Cohen *d*=0.81). As such, we are powered to detect the effect of our mindfulness intervention on plasma markers of amyloid. Other secondary variables of interest include behavioral and self-report measures of mind-wandering, including both laboratory- and EMA-based assessments of mind-wandering as well as the network strength of the DMN during the Gradual-Onset Continuous Performance Task. Given the pilot nature of the study, emphasis will be placed on the estimation of effect sizes and CIs for these effect sizes.

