### Study Procedures

Participants who meet the demographic criteria, along with criteria for the ECog Questionnaire, the T-MOCA, the IADL questionnaire, and MRI safety, are invited to the Clinical Neuroscience Laboratory at The Ohio State University for an initial in-person screening session. At this visit, visual acuity is assessed using the Snellen chart, and a blinded research assistant administers the UDS3-NB.

Participants meeting criteria for intact objective cognitive performance are then invited to a behavioral testing session at the Clinical Neuroscience Lab and a neuroimaging session at the Center for Cognitive and Behavioral Brain Imaging. During the behavioral session, a trained nurse from the Clinical Research Center at The Ohio State University collects the blood plasma sample, after which participants complete 2 behavioral measures of sustained attention and mind-wandering. As psychoaffective factors can influence perceived ratings of SCD, participants also complete a battery of questionnaires assessing stress (the Perceived Stress Scale [55]), depression (the Center for Epidemiologic Studies Depression Scale [56]), anxiety (the Beck Anxiety Inventory [57]), worry (the Penn State Worry Questionnaire [58]), quality of life (the World Health Organization Quality of Life–Brief [59]), and perceived racial discrimination (the Everyday Discrimination Scale [60]). We also administer the Motivation to Change Lifestyle and Health Behaviors for Dementia Risk Reduction [61] to quantify psychological and cognitive factors that influence engaging in health behaviors.

At the same session, participants receive training on EMA procedures and are provided with study-specific smartphones (Samsung Galaxy phones) to collect EMA data on mind-wandering, cognitive functioning, perceived stress, affect, and arousal for 5 days between sessions. Finally, structural and functional MRI data are collected at the neuroimaging session to quantify changes in the integrity of the DMN.

After completion of all assessment sessions, participants are randomized to either the iMBSR or the iLifeEd group with a 1:1 allocation ratio. All assessments will be readministered immediately following the 8-week intervention.

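### Uncontrolled ECog reductions count as supporting evidence of feasibility in people selected for a high ECog score, so regression to the mean can be credited to the program

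*Protocol article*

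**What the plan says.** The Primary Outcomes section defines high feasibility by two figures: 60 participants enrolled and "an attrition rate of no greater than 25" percent. It then adds that changes in subjective cognitive decline (SCD) will be examined, "with reductions on the ECog Questionnaire considered as evidence for feasibility of the intervention". The sentence names no size of reduction, no interval, no arm and no comparator. The acceptability criteria that follow all have numeric limits: a mean acceptability score above 3, a mean satisfaction score above 5, and at least half of participants completing six or more modules.

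The same questionnaire is the entry gate. Participant Eligibility states "we will use the previously validated cutoff score of 1.31 to recruit participants with SCD" and "Only participants with elevated scores (>1.31) will be invited for an assessment of objective cognitive performance".

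The abstract's Objective gives the measure a different role: "Secondary objectives include examining preliminary effects of each intervention on SCD".

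On timing, Study Procedures lists ECog among the criteria for being invited to the first in-person visit. The questionnaires it then names for the baseline behavioral session cover stress, depression, anxiety, worry, quality of life, discrimination and motivation, and ECog is not among them. Afterwards, "All assessments will be readministered immediately following the 8-week intervention".

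**The concern.** A change in symptoms is an effect of the program. It does not show whether people can be recruited, retained or taken through the modules. Placing it under primary feasibility conflicts with the abstract, which treats it as a secondary, preliminary effect.

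The placement matters more because of how people enter. A group chosen because one measurement was above a cutoff will on average score lower when measured again, in both arms, even if neither program does anything. With no comparator, this fall cannot be told apart from benefit. The Discussion itself faults earlier web-based mindfulness trials for lacking active controls, yet the ECog sentence makes no use of the active control that this trial has. What is at stake is a line in the primary report that presents a selection artefact as support for the program.

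**Working it through.** **The plan's own figure.** The ECog statement has no figure to reproduce. The nearest design figure is the margin of error for a within-group percentage with 30 per group: 1.96 × √(0.25/30) = 0.179, which agrees with the stated 18 points. So n = 30 per arm is used below.

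**Inputs from the protocol.** ECog cutoff 1.31; 30 per arm; 1:1 allocation after selection; 25% attrition tolerated (0.75 × 30 = 22.5, about 22 completers per arm).

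**Assumed inputs.** The article gives no ECog mean, SD or test-retest reliability for the source population, so these are varied. The screening score is taken as baseline and the intervention effect is set to zero.

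**Model.** Standardized scores are bivariate normal with reliability ρ, and people are kept if the first score exceeds c = (1.31 − source mean) / source SD. With λ = φ(c) / [1 − Φ(c)]:

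- expected fall = (1 − ρ) × λ, in source SDs
- variance of individual change = (1 − ρ)² × [1 − λ(λ − c)] + 1 − ρ²
- P(arm mean falls) ≈ Φ(expected fall / √(variance / n))

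**Worked case: cutoff at the source mean (c = 0), ρ = 0.8.**

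- λ = 0.3989 / 0.5 = 0.798
- expected fall = 0.2 × 0.798 = 0.160 SD
- variance = 0.04 × 0.363 + 0.36 = 0.3745; standard error = √(0.3745 / 30) = 0.112
- ratio = 0.160 / 0.112 = 1.43, so P = 0.92

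**Range, n = 30, no intervention effect:**

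| c | Share of source above cutoff | P(arm mean falls), ρ = 0.9 | P(arm mean falls), ρ = 0.6 |
|---|---|---|---|
| −1.5 | 93% | 0.57 | 0.64 |
| −1.0 | 84% | 0.64 | 0.77 |
| −0.5 | 69% | 0.74 | 0.91 |
| 0 | 50% | 0.84 | 0.98 |
| +0.5 | 31% | 0.92 | 0.999 |
| +1.0 | 16% | 0.97 | 1.00 |

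The expected fall runs from 0.01 to 0.61 source SD. With 22 completers per arm the range is 0.56 to 1.00.

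**Skewed scores.** The normal model may not suit a questionnaire score, so a right-skewed one was simulated: lognormal excess over a floor of 1, capped at 4, ρ 0.7 to 0.9, n = 30. For source means of 1.3 and 1.5 with SD 0.3 or 0.5, and for mean 1.7 with SD 0.5, the probability is 0.56 to 0.90. For mean 1.7 with SD 0.3, about 96% of the source already exceeds 1.31 and the probability is only 0.52 to 0.54.

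**Would within-arm significance help?** Not enough. If a two-sided 5% paired t-test were required in an arm of 30, a fall would be declared with no effect in 16% to 53% of trials at c = 0, and in 28% to 84% at c = +0.5.

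**Between-arm contrast.** Selection comes before randomization, so the expected fall from selection is the same in both arms and their difference has expectation zero.

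**The case against.** The strongest reply is that no decision depends on ECog. High feasibility is defined by enrolment and attrition alone, and ECog is added afterwards as something also examined. This stands. A reader might infer that the primary feasibility conclusion passes or fails on ECog, or that any reduction however small is a formal criterion. The document does not say so. The second is only a reading of an unquantified sentence.

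A second reply concerns timing. That change starts from the selecting score is inferred from a list that does not name ECog. The list does not name ECog at follow-up either, although it must be given then. A repeat ECog before randomization, if the full protocol has one, would remove much of the regression to the mean. This also stands, and the figures are conditional on it. Such a repeat would not supply a comparator or settle whether the measure is primary or secondary.

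Third, Data Management and Analysis plans mixed models with effect sizes and intervals for preliminary effects and other secondary outcomes, and the exact contrast for one supporting measure may be in a fuller document. That is fair, but the article does not connect those models to the ECog feasibility sentence, and what that sentence does state already gives the measure the wrong role.

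Fourth, the authors leave efficacy claims to later-stage studies, and the abstract asks about effects of each intervention, which a between-arm contrast does not answer. This limits the consequence and is a reason to keep within-arm changes as description. It does not make an uncontrolled fall evidence of feasibility.

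**Conclusion.** The concern holds in a limited form. The article counts uncontrolled reductions on the selection instrument as supporting evidence of feasibility under Primary Outcomes, and elsewhere treats the same effect as secondary. That conflict rests on the text alone.

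The size rests on assumptions: the screening ECog is the baseline, there is no intervention effect, and the source mean, SD and reliability are as varied above. A fall in a 30-person arm is then more likely than not, at about 56% to 100% where the cutoff excludes at least a modest share of the source. It is about 92% with the cutoff at the source mean and reliability 0.8, against 50% with no regression to the mean.

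A reader might infer that the ECog statement could hardly ever fail. The documents do not support that across the plausible range: if nearly all volunteers already exceed 1.31, the probability is only slightly above one half. The enrolment, attrition and acceptability thresholds are untouched.

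**What to change.** Delete the ECog sentence from the feasibility definition and list ECog change as a secondary, preliminary-effect outcome, in line with the abstract. Base any statement about benefit on the iMBSR minus iLifeEd difference at follow-up, adjusted for baseline ECog, with a 95% CI. Within-arm changes may be shown descriptively with a caution about regression to the mean. State which ECog administration is the baseline.

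The contrast removes the selection effect in expectation, provided attrition does not differ by arm, so completion by arm should be reported beside it.

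The cost is a change of wording, one model, and the loss of one favourable-looking supporting criterion. No new data are needed. The Results section says that analysis scripts are final but that analyses start only after all participants have finished, so the change can still be made and dated before outcomes are analysed.

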## Methods

### Study Design

The primary goal of our iMBT trial is to examine the feasibility and acceptability of the internet-based, asynchronous mindfulness-based stress reduction (iMBSR) program using a Stage I study design proposed in the National Institutes of Health (NIH) Stage Model [38]. Pilot studies are foundational for large-scale efficacy studies and help assess recruitment potential, delivery of the intervention, adherence and acceptability, barriers to compliance, and potential safety issues before the launch of large clinical trials [39-41]. These studies can also be used to generate estimates of a treatment’s effects and its variance and covariance to provide necessary data for large-scale trials [42]. For this RCT, we are recruiting a sample of adults with SCD, and participants are being randomized into 1 of 2 groups: iMBSR or iLifeEd. We are collecting data on the feasibility and acceptability of the program using a priori defined criteria. Additionally, blood plasma will also be collected before randomization and after 8 weeks of training to determine the effect of mindfulness training on Aβ_42_/Aβ_40_ ratio and p-tau217. To examine the preliminary effects of the iMBSR program on brain health, neuroimaging sessions will also be completed at both time points with the strength of the DMN serving as the measure of neuronal health. Participants will additionally complete computerized measures of sustained attention, EMA of mind-wandering and cognitive functioning, and several self-report questionnaires to assess their psychosocial profile. Figure 1 illustrates the timeline of assessment and intervention sessions for the ongoing clinical trial.

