## Results

This study was funded by the National Institute on Aging in April 2024. Phase I focused on iterative development of the 2 programs based on focus group feedback. Recruitment for the Phase II RCT (iMBT) began on June 13, 2025, and is ongoing. As of December 1, 2025, we have 31 participants randomized into the study: 15 participants have been randomized to the iMBSR group, and 16 participants have been randomized to the iLifeEd group. We anticipate that recruitment will end in September 2026, with all 60 participants randomized by that date. Although data analyses will begin after all participants have completed the intervention and assessment sessions, all analysis scripts have been finalized, and data reduction and processing are ongoing. We expect to complete the processing and analysis of the primary outcome variables by March 2027, with a targeted manuscript submission date of June 2027.

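### As printed, the acceptability criterion is reversed: on the stated 1-5 scale, a mean above 3 signals disagreement, yet it is labelled high acceptability

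*Protocol article*

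**What the plan says.** Under Sample Size and Power, the protocol article states: "Our primary outcome variables for this study are the feasibility and acceptability of the protocols". Under Study Design it adds: "We are collecting data on the feasibility and acceptability of the program using a priori defined criteria". The criteria themselves are under Primary Outcomes:

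- **Instrument:** "Acceptability will be measured using the Acceptability of Intervention Measure".
- **Scale:** 1 to 5, "ranging from “completely agree” to “completely disagree".
- **Success rule:** "with high acceptability defined as an average score greater than 3".

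The same paragraph sets two neighbouring criteria. Satisfaction is rated 0 to 10, "ranging from “not at all” to “extremely” scale", and is high when the mean exceeds 5. Participation is high when at least half of participants complete six or more modules.

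The Results section reports 31 of 60 participants randomized by December 1, 2025, and says that "all analysis scripts have been finalized", with analysis to begin once everyone has finished.

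**The concern.** The cutoff treats larger scores as better, whereas the anchors, in the order printed, make larger scores worse. A program whose participants agree that it is acceptable would miss this criterion, and one whose participants disagree would meet it. The satisfaction criterion in the same paragraph runs in the usual direction, so as printed the two measures point opposite ways.

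This matters because it is a decision threshold for a primary outcome, and the Discussion makes the feasibility and acceptability of the mindfulness program the main hypothesis. Readers will hold the trial to the published criterion. If the form carries the printed anchors and the final script applies a mean above 3, the script gives the wrong answer. If the form carries the opposite anchors, the article is wrong, and a later unexplained correction could look like a primary criterion changed after the data were seen.

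**Working it through.** The cutoff has no sample size, power or error rate behind it, so there is no figure of the plan's to reproduce. The check is whether the stated rule classifies response patterns as its label implies.

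**Inputs, all from Primary Outcomes:** scale 1 to 5; first-listed anchor full agreement; last-listed anchor full disagreement; rule mean > 3.

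**Which number goes with which anchor.** The article attaches no numbers to the two anchors. Two other scales show its convention. The 0-10 satisfaction scale in the same paragraph lists its low end first. The momentary-assessment scale under Mind-Wandering Prompts prints its numbers, 0 for the lowest category and 4 for the highest, again low end first. On that convention 1 is full agreement, 5 is full disagreement and 3 is the midpoint.

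**Applying the rule to 30 participants, one group's planned size.** Reversing the anchors turns a score x into 6 − x, so the mean m becomes 6 − m.

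| Responses | Mean, anchors as printed | Mean > 3? | Mean, anchors reversed | Mean > 3? |
|---|---|---|---|---|
| All completely agree | 1.0 | no | 5.0 | yes |
| All agree | 2.0 | no | 4.0 | yes |
| All neutral | 3.0 | no | 3.0 | no |
| All disagree | 4.0 | yes | 2.0 | no |
| All completely disagree | 5.0 | yes | 1.0 | no |
| 24 agree, 6 disagree | 2.4 | no | 3.6 | yes |

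The last row as printed is (24 × 2 + 6 × 4) / 30 = 72 / 30 = 2.4; reversed, it is 6 − 2.4 = 3.6.

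**Extent.** Since 6 − m > 3 exactly when m < 3, the printed rule and its mirror image give opposite answers for every m other than 3. At m = 3 neither declares success.

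**Equivalence of the repairs.** Keeping the printed anchors and requiring a mean below 3 gives the same classification in every row as reversing the anchors and keeping a mean above 3.

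**The case against.** The strongest reply is that this is a slip in describing an instrument and the decision rule itself is sound. Calling scores above 3 high acceptability shows that higher was meant to be better, and the simplest repair leaves the cutoff alone and swaps the anchor words. The article never pairs a number with either anchor, and the item wording and scoring key are not shown, so the inversion is an inference. The measure is also only one acceptability criterion. Satisfaction and module completion run in the expected direction, and a misdirected score would clash visibly with them. Nothing is known about how the final scripts score the measure, and any scoring error could be undone afterwards by taking 6 − x.

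Much of this stands. A wrong anchor order is the likeliest cause. The inversion applies to this criterion and does not by itself settle the overall acceptability conclusion, since the article gives no rule for combining the criteria. Whether the script is affected is unknown.

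None of it rescues the printed rule. The anchors and the cutoff are incompatible when read in order, as the article's other scales are read, and no reverse scoring, negatively worded item or numeric key is stated that would reconcile them. Nor is this a detail left to a fuller document: the article states the rule, and states it inconsistently.

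**Conclusion.** The concern holds. As written, the success threshold on the Acceptability of Intervention Measure is fully inverted: a mean of 1.5, strong agreement, fails, and a mean of 4.5, strong disagreement, passes. Only a mean of exactly 3 is classified the same either way.

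Two assumptions carry this: the anchors are numbered in the order listed, and the items are worded so that agreement means the program is acceptable. The first fits the article's other scales, and the second is natural for a measure with this name. The finding concerns the printed rule; it does not show that the form or the script is wrong. Because the threshold decides a criterion of a named primary outcome, it must be corrected before the analysis.

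**What to change.** 1. Check the form participants actually receive and the scoring script: the number attached to each anchor, the item wording, any reverse scoring, and the direction of the comparison.
2. Restate anchors and cutoff in one sentence that matches the form:
   - if 1 is complete disagreement and 5 complete agreement, correct the anchor order and keep a mean above 3;
   - if the form is numbered as the article implies, either reverse-score the items (6 − x) and keep a mean above 3, or set the criterion at a mean below 3.
3. As a precaution, confirm that everyone assessed so far saw the same anchors; nothing in the article suggests otherwise.
4. Date and document the correction before analysis begins, so that it cannot be taken for a change made after seeing results.

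The cost is one sentence and a script check. No new data are needed, and sample size and randomization are unaffected.
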